**Fig. 1 Fig1:**
[figure not shown]
Study design

**Table 1 Tab1:** Outcome measures

Outcomes	Participant Survey measurement points				Analysis metric		Measures
	T1		T2	T3			
	*Baseline*	*Exit*	*3 month follow-up*	*6 month follow-up*	*Change from baseline to follow-up*	*Follow-up value only*	
*Primary outcomes for all participants*							
Reproductive Coercion in past 3 months	X		X	X	X		RC Scale (RCS; 9 items) [25] (binary)
Physical IPV and Sexual IPV in past 3 months	X		X	X	X		Conflict Tactics Scale-2 (CTS2; 7 items) [26] (binary) Sexual Experiences Survey (1 item) [27] (binary)
Uptake of female controlled contraceptive method		X				X	Self-report (1 item)
*Secondary outcomes for all participants*							
Incident and unintended pregnancy past 6 months			X	X		X	National Survey of Family Growth (NSFG; 1 item) [28, 29] (binary)
Self-efficacy to utilize contraceptives in the face of RC	X		X	X	X		Investigator-developed (4 items) [23, 24] (summary score)
Knowledge of IPV services					X		Investigator-developed (4 items) [23, 24] (summary score)
Reduced acceptability of RC and IPV	X		X	X	X		Investigator-developed (8 items) [23, 24] (summary score) Kenya Demographic and Health Survey (DHS) (7 items) [30] (summary score)
*Secondary outcomes for those reporting RC and/or IPV at baseline*							
Covert use of contraceptives in the face of RC in the past 3 months	X		X	X	X		WHO Multi-country Study on Women’s Health and Domestic Violence against Women (1 item) [10] (binary)
Utilization of IPV services among those reporting IPV in the past 3 months			X	X		X	Investigator-developed (8 items) [23, 24] (binary)
Leaving a relationship because it felt unsafe or unhealthy among those reporting RC or IPV in the past 3 months			X	X		X	Investigator-developed (1 item) [23, 24] (binary)

All measures were adapted for use in the current study via cognitive interviews with Kenyan contraceptive care patients and providers

## Methods

### Kenyan country context

Similar to many other LMIC contexts, unintended pregnancy is high in Kenya, with 25.4% of births being mistimed and 10.3% unwanted [30], and the more than 2 in 5 women reporting IPV in the country are at 70% increased odds of unintended pregnancy as compared to their same age peers [31]. More than 1 in 3 (36%) women report currently using a modern form of contraception [31]. Although no previous quantitative studies of RC have been conducted in Kenya, our qualitative formative research among women and girls seeking contraceptive services suggested that RC and IPV are highly prevalent in this context, and that RC appears to pose a major barrier to successful contraceptive use [32].

### Setting

Participants for this study will be recruited from private, community-based health clinics in the greater Nairobi area, owned and operated by Family Health Options Kenya (FHOK). FHOK is a local non-governmental organization (NGO) that has provided sexual and reproductive health service in the country for the past 50 years [33]. These community-based clinics provide comprehensive healthcare including contraceptive counseling, and offer a broad range of contraceptive methods. All FHOK clinics adhere to the Kenyan Ministry of Health (MOH) contraceptive counseling guidelines [33]. All six FHOK clinics located in slum and non-slum areas within and around Nairobi were selected to participate in the adaptation and evaluation of ARCHES. As the capital of Kenya and one of the largest cities in Sub-Saharan Africa, Nairobi has multiple local GBV support services available for women and girls at low to no cost [34].

### Description of intervention

#### Adapting ARCHES to the Kenyan context

Adaptation of the U.S.-based ARCHES model took a participatory and stepwise approach; details of the U.S.-based ARCHES intervention and evaluation findings are reported elsewhere [23, 24, 35]. First, formative research was conducted to understand specific forms of RC experienced by Kenyan women and girls seeking contraceptive services, strategies they used to cope with RC, and how these experiences were or were not addressed in the context of the health system. Qualitative data were collected in April 2017 from four of FHOK’s community-based clinics in the Nairobi area; including focus group discussions and in-depth interviews with women and girls aged 15 to 49 years-old. Semi-structured interviews with contraceptive service providers and clinic managers were conducted to understand providers’ experiences with patients reporting RC and IPV, and to identify further areas for adaptation and integration. Detailed methods and findings for this qualitative study are reported elsewhere [32].

Based on the results from the formative research and existing contraceptive care practice, the original ARCHES model was revised, and new materials and protocols were developed from June to October 2017. The study team workshopped the materials and protocols in weekly meetings with a consortium of local and IPPF GBV specialists and FHOK health providers. Through this process, adapted materials and protocols were further modified to fit within existing provider practices and responsibilities, and utilized pre-existing materials and protocols whenever possible. Additionally, materials for patients were reviewed via cognitive interviewing with a small convenience sample of women and girls seeking contraceptive services from FHOK. Once materials were further revised based on patient responses, a workshop was held with four FHOK providers to maximize the feasibility and acceptability of refined protocols via simulated counseling role-plays.

The adapted ARCHES program was then piloted in two FHOK clinics in slum neighborhoods of Nairobi. Five providers from the two facilities received a 3-day training on the adapted ARCHES clinical protocols and materials. Providers subsequently administered ARCHES to women and girls seeking contraceptive services for a 3-month period. Patients receiving ARCHES completed pre- and immediately post-intervention surveys to assess fidelity and quality of the intervention, as well as their perceptions of relevance, acceptability, and potential efficacy of this approach. Semi-structured interviews were conducted with the five trained providers to understand barriers and facilitators to implementation, and their perspectives on the acceptability and utility of the intervention to improve the reproductive autonomy of women and girls. Findings from the pilot indicated the feasibility of implementation of the intervention, and high levels of acceptability among providers and patients, along with suggestions for minor refinements to further facilitate faithful implementation [36]. Based on these findings, intervention protocols and materials were finalized for study implementation. The final adaptation included printed materials to aid providers in their implementation of ARCHES clinical protocols, patient education materials, a waiting room poster, a palm-sized educational booklet, as well as facilitator and provider training manuals and a training slide deck.

#### ARCHES intervention for implementation in Kenya

The final intervention resulting from this adaptation process retains the three primary ARCHES strategies designed to educate and empower women and girls regarding contraceptive use in the face of male partner and family opposition, identify and address IPV and RC, and reduce unintended pregnancy (see Fig. 2. Conceptual model) which are universally delivered to all women and girls during private, contraceptive counseling.

**Fig. 2 Fig2:**
[figure not shown]
Conceptual model

In the ARCHES Kenya adaptation, all women and girls first receive comprehensive counseling and education on a broad range of contraceptive methods, and are asked about their pregnancy and contraception history and desires. Integrated within this otherwise standard contraceptive counseling is education on RC and contraceptive methods that may be used with a low risk of detection or interference from male partners or family members (i.e., contraceptive methods that may be used covertly, and strategies to reduce the likelihood of detection when using these methods) if they or someone that they know is facing RC. The specific strategies for reducing risk of detection included in ARCHES counseling are those that local women reported utilizing in the formative research [32]. Messages that destigmatize RC and affirm a woman’s right to use contraception, regardless of opposition, are also integrated.

The second ARCHES element involves providers offering an opportunity for a female patient to disclose and discuss their experiences of RC and IPV. Messages normalizing and destigmatizing RC (e.g., “Many of our patients have men or family members in their lives that make it difficult for them to use contraception.”) are delivered, followed by three standard screening questions regarding IPV (physical, sexual and emotional) and two standard screening questions regarding RC (pregnancy coercion and birth control sabotage). This element is designed to be a natural extension of the initial contraceptive counseling facilitated by the trust developed between the patient and provider during that initial discussion. ARCHES providers are trained to respond in a supportive and validating manner, and to never coerce or pressure a patient in any way to disclose either IPV or RC. This approach acknowledges that many women and girls do not disclose abuse to providers, or feel that is safe or appropriate to seek help from providers for GBV [37–39]. Women who do disclose IPV are offered to be connected by the provider via phone to a trained counselor from a local GBV survivor support agency at the close of their clinic visit (i.e. a “warm referral”); this approach has been shown to reduce barriers to referral uptake (trust of service providers, perception that services are not appropriate for their situation) [40, 41].

The final element of the model is offering all women and girls, regardless of disclosure, palm-sized educational booklets (available in English and Kiswahili) to take for themselves or to share with other women and girls in their communities. This booklet provides information about RC and IPV (with questions to reflect on personal GBV experiences), contraceptive methods that can be used with a low risk of detection, and contact information for local IPV support services. In U.S.-based efficacy trials, these educational booklets were highly effective tools for women to disseminate information and resources on GBV with other women in their families and communities [23, 24].

Due to the potential harm to patients that may result from discussion and disclosure regarding RC and IPV, providers are trained to always prioritize patient confidentiality, and to only administer ARCHES protocols when visual and auditory privacy can be ensured. If male partners or family members accompany a patient to the counseling room, providers must request to meet with the patient alone based on the premise of needing to ask potentially embarrassing questions. If the patient wishes for the accompanying male partner or family member to stay, or if they refuse to leave, providers are trained to only provide standard-of-care contraceptive counseling.

### Assignment of clinics to treatment conditions

As ARCHES facilitates changes in providers’ contraceptive service delivery to all female patients seen, individual random assignment of patients is not possible. Instead, assignment at the clinic level is required. All FHOK community-based clinics within and around the Nairobi area were enumerated (*N* = 6) by UCSD researchers and assigned to treatment or control condition in matched-pairs (*n* = 3 intervention, 3 control) by the UCSD and FHOK, with pairings determined based on those clinics most closely matched on patient volume, patient characteristics (i.e. wealth, age, services sought), and community type (slum vs non-slum). Random assignment within pairs was not acceptable to program implementers due to the reduced feasibility of providing regular support to ensure faithful, high-quality implementation to providers in distal clinics; i.e., those clinics closest to FHOK headquarters in southeast Nairobi were more likely to be assigned to the treatment condition. Participants self-assign to the treatment or control condition based on the clinic they visit for contraceptive services and enroll into the study by Population Council research assistants (RAs). No blinding of participants or providers will occur.

#### Training of intervention site providers

FHOK contraceptive counseling providers at clinics assigned to implement the intervention will be trained to deliver the adapted ARCHES model via a 3-day training (6 h of instruction per day). The ARCHES training utilizes Social Cognitive Theory, increasing providers’ behavioral capacity and self-efficacy to deliver ARCHES and services for contraceptive patients experiencing GBV through education, observational learning (peer-based), and practice. The training curriculum includes: [1] education on GBV (inclusive of RC and IPV), including patient narratives gathered during formative research [2]; values clarification exercises to clarify and challenge provider attitudes that pose barriers to women- and patient-centered care via group discussion and reflection [3]; instruction on ARCHES clinical protocols and local GBV services; and 4) demonstrations followed by group practice via role-plays and peer coaching. GBV education and values clarification are completed on day one, and clinical instruction and practice occur on days two and three. Providers trained during the pilot period are trained as facilitators in a 1-day training-of-trainers (TOT) to increase sustainability and scalability of the model in Kenya and encourage peer-support to improve adoption of and fidelity to the intervention.

Post-training, providers will receive clinic-based weekly technical assistance sessions for the first 3-months of implementation.

#### Assessing fidelity to the intervention

Research staff will compile implementation data summary reports based on weekly analysis of patients’ exit survey data to track intervention fidelity. Implementation data summary reports will include patients’ reported receipt of each intervention element. These results will be used to inform technical assistance sessions. Implementation data summary reports from control clinics will also be used to detect possible cross-site contamination.

#### Control condition

The three clinics assigned to the control condition will receive no additional training, thus, patients will receive standard contraceptive counseling based on their previous completion of training on contraceptive service delivery by the Kenyan MOH. If results of the ARCHES trial in Kenya prove the intervention efficacious, all control sites will receive ARCHES training and materials as part of FHOK’s plan to scale the intervention across its community-based clinics nationally.

### Outcome measures

All primary and secondary outcome measures are explained below and listed in Table 1.

### Primary outcomes

#### Reproductive coercion (RC)

Recent (prior 3 months) experience of RC will be assessed using a 9-item scale on specific RC behaviors including pregnancy coercion (e.g. “Has a male partner ever tried to force or pressure you to become pregnant when you did not want to be pregnant?”), and birth control sabotage (e.g. “Has a partner ever destroyed, hidden, or taken away your family planning method?”). RC is assessed primarily as a binary (yes/no) outcome based on a positive response to any RC experiences. Additionally, a summary score of the number of RC items experienced (Score 0–9) will be assessed in exploratory analyses. Items for this measure were adapted from those in the RC scale developed in the U.S. (Cronbach alpha = 0.74) [25] based on formative research and cognitive interviewing.

#### Physical and sexual intimate partner violence (IPV)

Recent (prior 3 months) experiences of physical IPV will be measured using an adapted version of the injury subscale of the Conflict Tactics Scale 2 (CTS-2) [26]. Physical IPV is assessed as a binary measure (yes/no) based on at least one positive response to a 6-item question series experiencing any of the included physically violent behaviors from an intimate partner (i.e. Has a male partner ever … pushed you, shaken you, or thrown something at you, slapped you, twisted your arm or pulled your hair, hit you with his fist or something that could hurt, kicked, dragged, or beaten you up, choked or burned you). Recent (prior 3 months) experiences of sexual IPV will be measured using a single item modified from the Sexual Experiences Short-Form Survey, “Has a male partner ever forced you to have sex or do something sexual when you didn’t want to?” [27].

#### Uptake of a modern contraceptive method

Report of receiving a modern contraceptive method during the clinic visit (binary, yes/no) will be assessed using a single item, “Did you receive a family planning method today from your provider?” with confirmation provided via a follow-up question regarding which method they received from a list of all available methods (i.e. IUD, implants, injection, contraceptive pills). The patch, vaginal ring and female condom are not included as they are not commonly utilized or available methods in this setting. Additionally, because the ARCHES intervention focuses on increasing uptake and understanding of female controlled contraceptive methods that are easy to use discretely to reduce RC, the male condom will be excluded from this measure.

### Secondary outcome measures

#### Incident pregnancy and unintended pregnancy

Incident pregnancy (prior 6 months; binary, yes/no) will be measured via one self-report item asking how many times the client had been pregnant in the past 6 months including stillbirths, miscarriages, and abortions. The single-item measure for 6-month unintended pregnancy was adapted from a 3-item assessment from the National Survey of Family Growth (NSFG) [28, 42]. The question is “At the time you became pregnant, did you want to become pregnant then, did you want to wait to become pregnant at a later date, or did you not want any more children?” Women who have never been pregnant will be considered to have not had an unintended pregnancy. Incident and unintended pregnancy within the past 6-months will be measured at follow-up visits only (T2 and T3). Unintended pregnancy (binary, yes/no) will be included as an exploratory outcome as the study will not be powered to detect a significant effect for this lower-prevalence outcome at alpha <.05.

#### Self-efficacy to use contraceptives, including in the face of RC

Self-efficacy to utilize contraceptives, including in the face of RC will be assessed using four items on participants’ confidence in their ability to successfully use a contraceptive method, including in the face of RC (e.g. “How confident are you that you could talk to your partner about your family planning use?”, “How confident are you in your ability to use family planning even if your partner tries to interfere?”). Participants are asked to rate their confidence regarding each statement on a 3-point Likert scale (Strongly agree, somewhat agree, disagree). The outcome will be modeled using a sum score (range 0 to 8). This scale, utilized in the U.S. ARCHES studies (Cronbach alpha = 0.72) [35], was modified for the Kenyan context based on formative research.

#### Acceptability of RC and IPV

Acceptability of RC will be assessed via an 8-item scale. Participants will be asked to endorse if, in their opinion, it is acceptable for husbands or male partners to enact different forms of RC (e.g. “force or pressure women to become pregnant or make it difficult for them to use family planning,” “throw away, destroy, hide, or otherwise interfere with a woman’s family planning method”) in a variety of situations (e.g. “if he wants more children than his partner”, “if she is experiencing side effects he does not like”). This Demographic and Health Survey (DHS) [30] wife-beating justification scale was modified to reflect acceptability of RC, and was piloted via cognitive interviewing. Acceptability of IPV will be assessed via 7 questions adapted from the DHS scale referenced above. Participants will be asked to endorse if, in their opinion, it is acceptable for husbands to beat their wife in a variety of situations (“she goes out without telling him,” “she argues with him,” “she burns the food”). Two additional situational question items will be added to the original scale that are relevant to RC (“she refuses to get pregnant,” “she uses family planning without his knowledge”). Participants are asked to endorse if they agree or disagree with the above statements. Question items will be added up for each scale (1 = agree; 0 = disagree) for a summary score where higher scores equate to attitudes more accepting of RC and IPV (maximum score 8 for RC; 7 for IPV).

#### Awareness of IPV services

To assess awareness of local services for women and girls experiencing IPV, participants will be presented a list of four local IPV support service agencies and asked whether they, “think a woman experiencing physical or sexual violence from her male partner could get help” at each one, with responses of yes, no, or don’t know. A summary score is calculated with one point per resource selected "yes" for a maximum score of 4. A similar list, utilized in the U.S. ARCHES studies (Cronbach alpha = 0.80) [35], was adapted to the Kenyan context based on the IPV services available in Nairobi.

#### Secondary outcome measures for those reporting IPV or RC at baseline

In addition to the outcomes above, three additional outcomes will be assessed among women and girls reporting ever experiencing IPV and/or RC at baseline, as this group is hypothesized to receive the greatest benefit from the ARCHES intervention.

#### Covert use of contraceptives among those reporting RC

Participants will be asked if they, “have ever used family planning without telling a male partner?” and a follow-up question establishes whether this covert use was within the past 3 or 6 months. Analyses of this outcome will be limited to those reporting ever having experienced RC at baseline.

#### Utilization of IPV services among those reporting IPV

Participants who report ever experiencing IPV at baseline will be asked whether they contacted or visited any local IPV support service agency in the past 3 and 6 months from the same list presented for awareness of IPV support services (see above). This will be modeled as a binary outcome, with participants who have called and/or visited any of the services being coded as having utilized IPV services.

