### Data analysis

We will adopt a difference-in-differences approach utilizing a multilevel, mixed-effects generalized linear regression, with logistic specifications for binary outcomes and linear specifications for continuous or scale outcomes, to evaluate associations between ARCHES intervention exposure and primary and secondary outcomes overtime. Longitudinal models will have fixed effects including time (baseline or follow-up), treatment arm, clinic, selected covariates, and a time and treatment interaction to indicate the treatment effect. These models will also take into account clusters (i.e. clinics) and clustering within clinics using nested random effects specifications to account for repeated measurements over time of individuals nested within clusters. The comparisons of outcomes at a single time point (e.g. immediately post-intervention) will use a similar multilevel mixed-effects regression approach, with single-level random effect specifications only for clinic, and only a fixed treatment effect (rather than time by treatment comparison). Final analyses will adjust for potentially relevant covariates (age, parity, food insecurity within the past 30 days, marital status, highest level of education attended, language of survey administration), in addition to time and treatment condition. Descriptive and bivariate analyses will be used to assess frequencies of and differences in demographics by treatment and loss to follow-up. Any characteristics identified as significantly associated with treatment or loss to follow-up at the *p* < 0.20 threshold will be considered as potential covariates (fixed effects) in adjusted models assessing effects of the intervention. Backwards selection at *p* < 0.20 will be used to finalize inclusion of potential covariates in regression models. Collinearity of covariates will be assessed, and highly collinear covariates may be removed from final models.

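### Use of IPV services is compared at follow-up only, so in this non-randomised design a between-arm difference in continuing use cannot be told apart from an ARCHES effect

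*Protocol article*

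**What the plan says.** **Population and question.** Under *Utilization of IPV services among those reporting IPV*, women with any lifetime IPV reported at baseline "will be asked whether they contacted or visited any local IPV support service agency in the past 3 and 6 months".

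**Coding.** The outcome is binary, with "participants who have called and/or visited any of the services being coded as having utilized IPV services". New and continuing use are not separated.

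**Timing.** The Table 1 row "Utilization of IPV services among those reporting IPV in the past 3 months" is marked at the 3- and 6-month surveys, not at baseline, and its analysis metric is the follow-up value only. (The label could be read as limiting the group to recent IPV. I take the group from the text, which uses lifetime IPV.)

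**Model.** *Data analysis* plans difference-in-differences for longitudinal outcomes. Comparisons at a single time point get a clinic random effect and "only a fixed treatment effect (rather than time by treatment comparison"). The listed covariates are age, parity, food insecurity, marital status, education and survey language.

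**Allocation.** *Assignment of clinics to treatment conditions* states: "Random assignment within pairs was not acceptable to program implementers". Pairs were those "most closely matched on patient volume, patient characteristics (i.e. wealth, age, services sought), and community type (slum vs non-slum"). Within that scheme, "those clinics closest to FHOK headquarters in southeast Nairobi were more likely to be assigned to the treatment condition".

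**The concern.** Difference-in-differences is this trial's main statistical guard against non-random allocation, and it needs a baseline value. Service use has none. Demographic covariates and survey language do not measure earlier contact with an agency, and the planned screening of covariates at p < 0.20 cannot select a variable that was never collected.

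The group consists of women with lifetime IPV in a city that, according to *Setting*, has several GBV services at low or no cost. Some may already be in contact with an agency and stay in contact after the visit. If that share differs between the two sets of clinics, the difference enters the treatment estimate.

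Greater use of IPV services is one of the stated hypotheses, and warm referral is a core element of ARCHES. A positive finding would be cited in decisions on scale-up, and a null finding could hide a real effect.

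**Working it through.** **1. Is follow-up-only measurement forced by the outcome?** Compare the rows of Table 1.
- Method uptake happens at the visit, and pregnant women are excluded at enrolment, so a follow-up value is natural for those outcomes.
- Covert use is a recurring behaviour with a recall window. It is measured at baseline and analysed as change.
- Awareness of IPV services uses the same agency list and is analysed as change from baseline.
- Service use is a recurring behaviour asked from that list, but has no baseline value.

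Nothing in the outcome prevents a baseline question.

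**2. Where does the look-back window fall?** *Time points* puts the 3-month survey at 12–16 weeks after the visit. Taking 6 months as 26 weeks, a 6-month question asked then reaches back 26 − 16 = 10 to 26 − 12 = 14 weeks before the visit. The text does not tie each window to a survey. If the 6-month window is used only at the 6-month survey (24–26 weeks), the overlap is 0 to 2 weeks.

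**3. Stated figures.** The protocol gives no rate, effect size or power for this outcome. Its sample size rests on RC. From 17.1% and OR 0.4 the second rate is 7.62%, and the usual two-proportion formula gives 189 per arm. The design effect is 1 + ((1 + 0.5²) × 68 − 1) × 0.001 = 1.084, so 189 × 1.084 = 204.9 against the stated 204. Then 408 / 0.75 = 544, as stated. This point changes none of these figures.

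**4. Illustrative size.** Inputs from the protocol are 600 enrolled, 75% retention at 6 months, and IPV in more than 2 in 5 women nationally (taken as 40%). Then 600 / 2 × 0.75 × 0.40 = 90 women per arm.

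Assumed, with no source in the documents: *b*, continuing use from before the visit, and *n*, new use, equal in both arms so that ARCHES has no effect. Measured use is p = b + (1 − b) × n.

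| *b* control | *b* ARCHES | *n* | p control | p ARCHES | OR |
|---|---|---|---|---|---|
| 5% | 5% | 3% | 7.85% | 7.85% | 1.00 |
| 2% | 5% | 3% | 4.9% | 7.85% | 1.64 |
| 5% | 10% | 0% | 5.0% | 10.0% | 2.11 |
| 5% | 10% | 3% | 7.85% | 12.7% | 1.71 |
| 5% | 10% | 5% | 9.75% | 14.5% | 1.57 |
| 5% | 15% | 3% | 7.85% | 17.55% | 2.50 |
| 10% | 5% | 3% | 12.7% | 7.85% | 0.59 |

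For example, in the fourth row: (0.127 / 0.873) / (0.0785 / 0.9215) = 1.71.

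**5. Chance of a false positive, 90 per arm.** With *n* = 0, a pooled z-test that ignores clinics rejects (two-sided) about 24% of the time at 10% versus 5%, and 63% at 15% versus 5%. With *n* = 3%, the chance of a significant result favouring ARCHES is 19% and 50% for the same imbalances, against a nominal 2.5%.

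**6. Equal continuing use.** Suppose ARCHES truly raises new use from 3% to 10%. With *b* = 0 the OR is 3.59. With *b* = 5% in both arms it is (0.145 / 0.855) / (0.0785 / 0.9215) = 1.99.

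**The case against.** **Continuing users are counted in both arms.** A reader might infer that every woman already using a service is credited to ARCHES. That is not so. Only a between-arm difference creates a spurious effect, and its direction is unknown. Equal use dilutes. This objection stands, and the point is limited accordingly.

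**Allocation was not by location alone.** A reader might infer that geography decided the arms. Clinics were first paired on volume, patient characteristics and community type; proximity then made assignment to ARCHES more likely. This stands too, although service use and access were not among the matching factors.

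**The link from headquarters to IPV services is unproven.** The stated reason for proximity is provider support. A phone call counts as use, which weakens any dependence on distance. Nothing in the protocol shows that prior use differs by arm. This stands: the documents show a missing safeguard, not a demonstrated bias.

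**The rejection rates rest on assumed imbalances and a test that is not planned.** Also fair. In place of the z-test's 24% and 63%, a Wald test on the log odds ratio gives about 20% and 58%, and a t-test on three versus three clinics of 30 women gives about 16% and 40%. At 7% versus 5% the Wald test rejects about 5% of the time. But the choice of test changes the rejection rate, not the bias in the odds ratio.

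**Most of the look-back falls after the visit, and awareness of the same agencies is analysed as change.** The first part limits the problem mainly to continuing use, apart from a 6-month question at the 3-month survey. The second would reveal a baseline difference in familiarity, but awareness is not use and does not enter this model.

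**Conclusion.** The point holds as a limitation of one secondary outcome in a subgroup. Use of IPV services has no baseline value in a trial that relies on baseline values to offset non-random allocation, so the planned contrast cannot separate an ARCHES effect from a pre-existing difference in continuing use. The bias could favour ARCHES or work against it.

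Its size cannot be known from the documents. Under the assumptions shown, it runs from none (equal use, no ARCHES effect, OR 1.0) to an odds ratio of about 1.7 to 2.1 when continuing use is 10% versus 5% and new use is 3% or zero; at 5% new use it is 1.57. The primary outcomes and the sample size are unaffected. The change is worth making because it is cheap.

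**What to change.** **For women still to be enrolled.** Ask the agency-use items at baseline (past 3 months) of women reporting IPV. Analyse use with the time-by-treatment model planned for RC, or adjust for baseline use. Adjustment is the simpler choice where the follow-up window is longer than the baseline window.

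**Look-back.** At each follow-up survey, limit the question to the period from the enrolment visit onward, and state which window belongs to which survey.

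**For women already enrolled.** At the 3- and 6-month surveys, ask whether contact with each agency used began before or after the enrolment visit, and analyse first contact after enrolment. State in the report that this removes continuing users but not clinic differences in access to services. It is therefore weaker than a baseline value.

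**Cost.** A few extra items at baseline for women reporting IPV, one follow-up item per agency contacted, and a survey amendment with its ethics review. The sample size does not change.
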